**Figure 2 fig2:**
[figure not shown]
The LIFUP intervention protocol.

#### Parameters

2.3.1

For the stimulation protocol in Group A (100 Hz TUS), LIFUP will be applied with the following parameters: Fundamental Frequency (FF):500 kHz, Pulse Repetition Frequency (PRF): 100 Hz, Pulse Width(PW):0.5 ms, Duty Cycle (DC):5%, Sonication Duration (SD):30 s, Number of Sonication:20, Spatial-peak Pulse-Average Intensity (ISPPA):14.39 W/cm (2), and Spatial-peak Temporal-Average Intensity (ISPTA):719.73 mW/cm (2). Peak rarefactional pressure:0.68 MPa. The pulse timing parameters of 100 Hz TUS are shown in Figure 3.

**Figure 3 fig3:**
[figure not shown]
Pulse timing parameters of 100 Hz TUS.

Under stimulation condition Group B, referred to as tb TUS following protocol (27), the parameters will be set as follows: FF of 500 kHz, PRF of 5 Hz, PW of 20 ms, DC of 10%, SD of 200 ms, with a total of 400 sonication. ISPPA is 7.19 W/cm (2), and the ISPTA is 719.73 mW/cm (2). Peak rarefactional pressure:0.48 MPa. The pulse timing parameters of tbTUS are shown in Figure 4. Group C will undergo the tbTUS protocol, but the transducer’s power supply will remain deactivated. In order to minimize possible sound-related confounds during TUS (28), white noise will be delivered to participants through earbuds while sonication is administered. The neural activity and safety of both stimulation protocols (100 Hz TUS and tbTUS) have been validated in several previous studies (19, 20, 27, 29). The energy levels employed in this study are well below the limits set by the U. S. Food and Drug Administration (FDA) for diagnostic ultrasound interventions through the human skull (mechanical index, MI ≤ 1.9; spatial-peak pulse-average intensity, ISPPA≤190 W/cm (2)) (30).

**Figure 4 fig4:**
[figure not shown]
Pulse timing parameters of tbTUS.

#### LIFU instrument

2.3.2

The LIFU signals were produced by a four-element ring array transducer (NeuroFUS Pro, DAPX-500, Brainbox Ltd., Cardiff, UK) featuring a 64 mm outer aperture diameter and radius of curvature. This transducer was connected to a programmable RF amplifier (Transducer Power Output System, TPO-203, Brainbox Ltd., Cardiff, UK) and driven at 500 kHz by a 4-channel power amplifier (Sonic Concepts). According to the manufacturer’s test results, the output power and phase of each element were precisely controlled to generate an in-water focal pressure of 948.7 kPa (equivalent to a pulse-average spatial peak intensity, ISPPA, of 30 W/cm (2)) at a focal distance of 53.6 mm. The measured -3 dB focal size in water was 19.5 mm (lateral) by 53.0 mm (axial). If the average skull attenuation (insertion loss) is −10 dB (31), the estimated intracranial acoustic parameters include a peak focal pressure of 300 kPa and an ISPPA of 15 W/cm (2). The actual insertion loss varies depending on individual patient skull characteristics. For precise targeting, transducer positioning was guided by neuronavigation (Brainsight, Rogue Research Inc.), with real-time tracking accounting for individual skull attenuation characteristics that inherently reduce the effective focal intensity.

#### Target

2.3.3

Based on foundational research involving DBS in non-human primates (32), clinical DBS case studies (33), mechanistic insights (34), and accumulated therapeutic experience (19, 20), the stimulation targets for this study are selected from the medial and intralaminar thalamic nuclei group of the ALL3 atlas (35). Specifically, these include the Reuniens nucleus (Thal_RE), the medial magnocellular portion of the mediodorsal nucleus (Thal_MDm), and the lateral portion of the mediodorsal nucleus (Thal_MDl), as well as the intralaminar thalamic nuclei (Thal_IL). The stimulation will target either the left or right side of the thalamus, in accordance with the anatomical references outlined in the ALL3 atlas (35).

The target acquisition process involves the following steps:Data conversion: Digital Imaging and Communications in Medicine (DICOM) data are first converted into the standardized Neuroimaging Informatics Technology Initiative (NIfTI) format.Segmentation: The segmentation function in SPM12 (36) is applied to each three dimensional (3D) T1-weighted MRI image to segment gray matter, white matter, and cerebrospinal fluid.Thalamic mask extraction and normalization: A thalamic mask is extracted from the ALL3 template and then normalized to the individual’s T1-weighted MRI for precise anatomical localization (demonstrative images are provided in Figure 5).

**Figure 5 fig5:**
[figure not shown]
The target of this study is delineated on the MNI template, with the red area specifically indicating the region of interest.

In cases where patients exhibit skull defects, LIFUP intervention may be considered on the intact side of the skull. However, the absence of skull can lead to a significant increase up to 50% in ultrasound energy at the target site. This amplification compromises the standardization, stability, and safety of the intervention. Therefore, LIFUP is not recommended for patients with large skull defects or those who have undergone cranioplasty involving metallic implants. Additionally, caution should be exercised when considering LIFUP for patients with implanted ventriculoperitoneal (VP) shunts for hydrocephalus.

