#### Exclusion criteria

2.2.2

Participants with significant/severe cardiac disease;Participants with a history of neurological illness prior to the current injury;Participants who are unable to safely undergo MRI scanning due to a severe infection;Participants with intracranial metal implants.

All patients will be recruited from the intensive care and rehabilitation wards. The study will be conducted from March 2025 to December 2025. Potential participants will be identified by reviewing electronic medical records within the hospital information system (HIS). Researchers will explain the details of the study to the patients’ legal guardians. Upon obtaining consent, a neurologist will evaluate each candidate based on the inclusion and exclusion criteria. Those who meet the eligibility requirements will be formally invited to participate in the study and will undergo a comprehensive neurological examination, followed by a rehabilitation assessment, prior to the intervention.

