#### Randomization

2.2.4

Randomization will be performed using the random number generation function in the R programming language (set.seed). All eligible participants will be randomly assigned to one of three groups in a 1:1:1 ratio: Group A (100 Hz TUS), Group B (tbTUS), and Group C (sham stimulation). To ensure allocation concealment and fairness, a randomization sequence will be generated by an independent researcher who is not involved in the trial’s implementation or outcome evaluation. The randomization sequence will be kept confidential and will not be disclosed to outcome assessors or statisticians. Baseline assessments will be completed after group assignment. Healthcare providers and therapists involved in the participants’ care, including acupuncturists and cognitive therapists, will remain blinded to group allocation to minimize bias.

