#### Simulations (k-Plan)

2.3.4

We will utilize k-Plan software to conduct our simulations, using a transducer model configured according to the physical properties of the NeuroFUS transducer and the phase settings specified for the TPO unit. Given the deep subcortical location of the left and right thalamus, we will simulate the ultrasound beam with a focal depth tailored to the target distance determined by Brainsight, which individually reflects the focal depth required for each participant’s anatomical structure. Transcranial simulations targeting the left or right thalamus will be performed for each participant. All patients will have undergone a cranial CT scan during their hospital stay, which will be used for default CT calibration. We will use 3D Slicer to co-register the head CT data with the participant’s T1-weighted MRI to ensure precise anatomical alignment. Following the simulation, relevant reports and results will be generated. Based on these outcomes, we will identify the optimal stimulus location. Subsequently, Brainsight software will be used to guide and implement the stimulation procedure in accordance with the simulation results. (Illustrative images are provided in Figure 6). The simulated images displayed in Figure 6 were generated using standardized neuroimaging templates. The MR template employed in k-Plan corresponds to the ICBM 1522009c Nonlinear Symmetric template (1 × 1 × 1 mm resolution; filename: mni_icbm152_t1_tal_nlin_sym_09c.nii), as described by Fonov et al. (37). The CT template implementation follows the methodology outlined by Rorden et al. (38). For additional technical details regarding these planning images, please refer to the official k-Plan documentation available at.^1^

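### Large skull defects, and possibly metallic cranioplasty, are advised against in section 2.3.3 but not clearly excluded in section 2.2.2, so such a patient can be randomised.

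*Protocol article*

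**What the plan says.** Section 2.2.2 (Exclusion criteria) has four items: serious cardiac disease, earlier neurological illness, inability to have MRI safely because of a severe infection, and "Participants with intracranial metal implants". The same section has a neurologist judge each candidate against the listed inclusion and exclusion criteria, and those who pass are invited to take part. That list is the eligibility gate.

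Section 2.3.3 (Target, in the text below Figure 5) adds three statements of different strength:

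- For skull defects in general: "In cases where patients exhibit skull defects, LIFUP intervention may be considered on the intact side of the skull".
- For large defects and metal plates: "LIFUP is not recommended for patients with large skull defects or those who have undergone cranioplasty involving metallic implants". The reason given is that missing bone can raise the energy at the target by up to 50%, to the detriment of standardisation, stability and safety.
- For shunts: "caution should be exercised when considering LIFUP for patients with implanted ventriculoperitoneal (VP) shunts for hydrocephalus".

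On timing, section 2.2.4 (Randomization) says: "Baseline assessments will be completed after group assignment". Section 2.3.4 (Simulations) says: "All patients will have undergone a cranial CT scan during their hospital stay". The use it gives for that CT is calibration of the simulation; it does not mention eligibility.

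**The concern.** Two sections of one document answer the same question differently. On section 2.2.2, a patient with a large skull defect is eligible. On section 2.3.3, that patient should preferably not be sonicated. Followed as written, the protocol can randomise someone and then face a choice between treating against its own advice and taking a randomised patient off treatment.

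The first outcome is a safety inconsistency. The second is an exclusion after randomisation, which weakens the comparison that randomisation is meant to protect. It matters more if it falls unevenly. The energy argument in section 2.3.3 has no force in the sham arm, where section 2.3.1 keeps the transducer's power off, so someone who knew the allocation would have less reason to withdraw a sham patient than an active one. Skull defects and cranioplasty reflect the injury and its surgical treatment, so uneven removal could shift the arms in cause and severity of injury.

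**Working it through.** **Step 1. Set the two sections side by side.**

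| Feature | Section 2.3.3 | Section 2.2.2 | Conflict? |
|---|---|---|---|
| Large skull defect | Advised against | Not named | Yes |
| Metallic cranioplasty | Advised against | Covered only if a skull plate counts as intracranial | Ambiguous |
| Other skull defect | Intact side may be considered | Not named | No |
| VP shunt | Caution | Not named | No |

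One row is a clear contradiction, one is an ambiguity of wording, and two are not conflicts.

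**Step 2. Can the conflict surface after allocation?** Baseline assessments are completed after group assignment. Section 2.3 lists them as CRS-R, HD-EEG, SSEPs, fMRI, MRS and PET-CT, so none is aimed at the skull. Records are reviewed when candidates are identified (2.2.2), and a cranial CT exists from the hospital stay (2.3.4), although its timing relative to randomisation is not stated. A skull defect may therefore be known before allocation, but nothing written requires anyone to look for it or act on it by then.

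**Step 3. Can the handling differ by arm?** Section 2.3 gives two sessions to all three groups, section 2.3.4 simulates for every participant, and section 2.3.1 runs sham as the tbTUS procedure with the power off. No suitability or withdrawal rule depends on arm. Section 2.2.3 does allow withdrawal by the investigator, and the blinding text in 2.2.4 does not mention the person who operates the device. A route to uneven handling exists, but the article does not describe one.

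**Step 4. How much room does the sample size leave?** Inputs from section 2.2.3: effect size 0.40, power 0.80, corrected α = 0.0167, 22 per group, 15% allowance for dropout or exclusion, minimum 76, enrolment 78 (26 per arm).

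- Reproducing the totals: 3 × 22 = 66; 66 × 1.15 = 75.9, the stated 76; 66 / 0.85 = 77.6, the enrolled 78.
- Reproducing the group size: a repeated-measures ANOVA, between-group test, with two measurements and correlation 0.5 (both assumed, as the article gives neither) needs 17 per group at α = 0.05 (stated 18) and 22 at α = 0.0167 (as stated).
- After the allowance: 26 × 0.85 = 22.1 per arm, against 22 required.

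For illustration only, suppose a further share of patients were lost evenly across arms, beyond the 15%:

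| Further loss (assumed) | Left per arm | Nearest whole number | Power at α = 0.0167 |
|---|---|---|---|
| 0% | 22.1 | 22 | 0.82 |
| 5% | 21.0 | 21 | 0.80 |
| 10% | 19.9 | 20 | 0.77 |
| 20% | 17.7 | 18 | 0.71 |

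These rows show sensitivity; they are not an estimate. The article gives no prevalence for any of these features, and loss on anatomical grounds may already sit within the 15%.

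**The case against.** The strongest reply is that most of section 2.3.3 does not contradict the exclusion list. Shunts attract caution only, and a skull defect may be handled on the intact side. Metallic cranioplasty is arguably already excluded as an intracranial metal implant. Candidates come from medical records and are seen by a neurologist, and every patient has a cranial CT, so a large defect would probably be noticed before allocation. All of this stands, and it narrows the point to large skull defects plus one ambiguous item.

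A reader might go further and infer three things that the article does not support:

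- *That all three features are restrictions missing from the list.* The shunt and intact-side wording does not advise against sonication.
- *That affected patients would leave the active arms and stay in sham.* Planning and procedure are described alike for all arms and no arm-specific removal rule exists. This is a risk, conditional on the person judging suitability knowing the arm.
- *That the trial would fall well short of 22 per arm.* That needs an invented prevalence, and it counts exclusions twice if the 15% is then deducted as dropout alone.

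The reply does not remove the core. Both rules are printed in the article, so condensation from a fuller protocol does not explain the conflict, and an incidental chance of noticing a defect is not an eligibility rule.

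**Conclusion.** The point holds in limited form. The protocol contradicts itself on large skull defects and is unclear on metallic cranioplasty. As written, a patient whom section 2.3.3 advises against sonicating can pass section 2.2.2 and be randomised. Exclusion after randomisation is then possible; imbalance between arms is conceivable but not established.

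The number of patients affected cannot be derived from the article. What can be said is that the planned margin is thin (22.1 against 22 per arm) and that part of any such loss may already be inside the 15% allowance. The power figures rest on two assumed measurements with correlation 0.5 and on hypothetical extra losses. The contradiction itself rests on the text alone and needs none of these assumptions. It should be corrected because it touches safety and the repair is small.

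**What to change.** 1. Reconcile sections 2.2.2 and 2.3.3 so that one eligibility rule covers large skull defects and metallic cranioplasty, and say how the intact-side allowance and the shunt caution apply. Which clinical rule is adopted is for the sponsor to decide.
2. State that this rule is applied before randomisation, from the medical records and the cranial CT, and identically for all three arms including sham.
3. State that every randomised patient stays in the intention-to-treat analysis set, whatever treatment was received. This concerns the analysis set only and does not restrict any decision on treatment. It extends what section 2.2.3 already says about retaining data collected before withdrawal.

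The cost is wording in two sections and a record and CT check moved ahead of allocation. If a patient's CT has not yet been done, allocation waits for it. Recruitment may be slightly slower.

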#### Simulations (k-Plan)

2.3.4

We will utilize k-Plan software to conduct our simulations, using a transducer model configured according to the physical properties of the NeuroFUS transducer and the phase settings specified for the TPO unit. Given the deep subcortical location of the left and right thalamus, we will simulate the ultrasound beam with a focal depth tailored to the target distance determined by Brainsight, which individually reflects the focal depth required for each participant’s anatomical structure. Transcranial simulations targeting the left or right thalamus will be performed for each participant. All patients will have undergone a cranial CT scan during their hospital stay, which will be used for default CT calibration. We will use 3D Slicer to co-register the head CT data with the participant’s T1-weighted MRI to ensure precise anatomical alignment. Following the simulation, relevant reports and results will be generated. Based on these outcomes, we will identify the optimal stimulus location. Subsequently, Brainsight software will be used to guide and implement the stimulation procedure in accordance with the simulation results. (Illustrative images are provided in Figure 6). The simulated images displayed in Figure 6 were generated using standardized neuroimaging templates. The MR template employed in k-Plan corresponds to the ICBM 1522009c Nonlinear Symmetric template (1 × 1 × 1 mm resolution; filename: mni_icbm152_t1_tal_nlin_sym_09c.nii), as described by Fonov et al. (37). The CT template implementation follows the methodology outlined by Rorden et al. (38). For additional technical details regarding these planning images, please refer to the official k-Plan documentation available at.^1^

**Figure 6 fig6:**
[figure not shown]
Pressure maps derived from ultrasound modeling superimposed on the MRI image of the MNI template, which was obtained from k-Plan.

#### Procedure

2.3.5

Ultrasound transmission gel (Hainuohai, Qingdao Hainuo Bioengineering Co., Ltd., China) will be applied to each participant’s scalp to ensure optimal acoustic coupling. A gel pad (Jiangkangtang, Zhengzhou Kangyijian Medical Devices Co., Ltd., China) will be used in conjunction with the transducer probe. Care will be taken to eliminate any air bubbles between the transducer surface and the participant’s head, as these may interfere with ultrasound transmission. Neuro-navigation will be performed using Brainsight software (version 2.5.3, Rogue Research Inc., Montreal, Quebec, Canada) based on each participant’s anatomical T1-weighted MRI scan. The target lesion depth will be adjusted for each individual according to the simulation scheme generated in K-Plan. During the LIFUP sessions, the navigation software will be used to continuously identify and monitor the targeted stimulation regions. The software will also be used to locate sensor coordinates and detect any deviations from the predetermined focal point.

#### Safety assessments and follow-up

2.3.6

We will make sure to get approval from key family members before proceeding. In terms of safety, we will record important parameters such as heart rate, blood oxygen and blood pressure during LIFU intervention and imageological examination data collection. In addition, any adverse events that occurred to the patients during the course of the study will be recorded. Patients will undergo follow-up assessments using CRS-R at 1, 3, and 6 months after LIFUP intervention treatment, and if possible, re-examination of fMRI and EEG will be conducted.

### Outcome measures

2.4

The primary outcome of this study is the recovery of consciousness measured by CRS-R and CRS-R_index_. Secondary outcomes will include the assessment of neurophysiological changes through multimodal neuroimaging and electrophysiological measures (fMRI, MRS, EEG) to evaluate intervention efficacy and safety. Additionally, SSEPs and PCT-CT measurements will be obtained at both baseline and endpoint assessments. These measurements will provide valuable insights into the impact of the study and aid in further understanding the research findings. Any adverse outcomes or side effects will be documented throughout the treatment process.

#### Primary outcome detection (behavioral data evaluation)

2.4.1

CRS-R and CRS-R_Index_: at the individual level, the CRS-R will be used to evaluate the progress of patients with pDoC. The CRS-R comprises 23 items across six subscales that assess auditory, visual, motor, oromotor/verbal, communication, and arousal functions. Changes in patient status will be assessed by comparing pre- and post-treatment scores for each subscale. At the group level, the CRS-R_Index_ score will be used to evaluate behavioral reactivity across both intervention and control groups, as it is considered to provide a more representative measure of functional recovery. CRS-R assessments will be conducted at baseline, before the intervention, and after each treatment session to capture the best observed performance for each patient. For patients who undergo two sessions of LIFUP, scores will be averaged and included in the group-level analysis.

#### Secondary outcome detection (image and electrophysiological data assessment)

2.4.2

At baseline and following treatment of LIFUP, patients will undergo a series of MRI scans using a 3.0 T Siemens VIDA scanner (Siemens Healthineers, Erlangen, Germany) equipped with a 64-channel head coil. The experiment will acquire the following sequence of scans: T1-weighted imaging, BOLD fMRI, DTI, and 1H-MRS (see Supplementary material 1 for details). Previous psychophysiological interaction (PPI) analysis19 revealed a more complex change in connectivity between the thalamus and the rest of the brain during LIFU application. The primary objective of this study is to investigate potential changes in thalamocortical connectivity, particularly between the thalamus and prefrontal/parietal cortices, before and after intervention. Glx/GABA concentrations will be quantified using 1H-MRS. While prior studies24,25 have reported stimulation-induced Glx or GABA level changes in cortical regions, these findings remain largely restricted to superficial cortical areas. In this study, we aim to examine whether different stimulation parameters induce measurable changes in concentrations of Glx/GABA within the medial and intralaminar nuclei of the thalamus. This may provide further insight into the underlying neural mechanisms of recovery in patients with DoC.

Additionally, participants will undergo a head PET-CT scan using a Vereos PET-CT scanner (Philips, Netherlands). Each subject will receive an intravenous injection of fluorodeoxyglucose (FDG), dosed at 0.1 mCi/kg based on body weight. After injection, participants will rest quietly in a dimly lit room with eyes closed for 60 min before the scan. Regional changes in glucose metabolism may serve as direct indicators of treatment efficacy and help predict clinical outcomes. Similar metabolic investigations have been reported in studies focusing on the hippocampus (39) (more detailed information regarding fMRI and PET-CT procedures can be found in the Supplementary material 1).

SSEPs will be assessed during the baseline phase prior to stimulation of LIFUP. A follow-up SSEPs evaluation will be conducted 1 day post-treatment during the experimental phase. Drawing on previous protocols involving thalamic TUS stimulation in healthy individuals (40), SSEPs are proposed as a useful indicator for monitoring treatment efficacy and prognostic outcomes.

Both resting-state and task-related EEG recordings will be obtained once on the day before and once on the day after intervention of LIFUP. EEG serves as a critical diagnostic and prognostic tool in patients with pDoC. To date, no studies have systematically reported changes in EEG functional connectivity, complexity measures, or spectral power before and after treatment of LIFUP in this population. Additionally, task-evoked EEG responses following intervention of LIFUP have not yet been explored. This study aims to bridge this gap by investigating EEG-based changes in neural dynamics and connectivity associated with LIFUP, thereby offering new insights into its therapeutic mechanisms in pDoC (more detailed information on SSEPs and EEG protocols is provided in the Supplementary material 1).

